# Chinese herbal formula Tongxie Yaofang for diarrhea-predominant irritable bowel syndrome: study protocol for a randomized, multiple-blind, placebo-controlled trial

**DOI:** 10.1186/s13063-022-06142-x

**Published:** 2022-03-21

**Keywords:** Tongxie Yaofang, Chinese herbal medicine, Irritable bowel syndrome, IBS-D, Randomized controlled trial

## Abstract

**Introduction:**

Diarrhea-predominant irritable bowel syndrome (IBS-D) is a bowel disease with a high incidence. It significantly reduces the quality of life of patients and affects the patient's daily activities and mental health. No specific therapeutic medications for IBS-D have been found. Published clinical trials suggest that Chinese herbal formula Tongxie Yaofang (TXYF) for IBS-D may be effective. However, high-quality clinical evidence supporting its use in IBS-D is still lacking. This trial aims to evaluate the therapeutic effects and safety of TXYF for IBS-D in adults.

**Methods/design:**

A randomized, multiple-blind, placebo-controlled trial will be conducted. It will consist of an 8-week intervention followed by a 3-month follow-up period.

The target sample size is 96 IBS-D patients aged 18 to 65 years. The eligible participants will be randomly allocated to either TXYF or placebo group in a ratio of 1:1. Participants in the experimental group will take TXYF granules, while participants in the control group will be given TXYF placebo granules. The primary outcome will be the degree of IBS symptom severity measured using the scale of IBS symptom severity score. The secondary outcomes include: (a) stool frequency, and (b) stool consistency measured using the Bristol stool scale, (c) quality of life measured using the scale of IBS-quality of life, (d) anxiety measured using the self-rating anxiety scale, (e) depression measured by the self-rating depression scale, and (f) the safety of using TXYF and placebo. Safety monitoring and assessment will be undertaken throughout treatment.

**Discussion:**

Chinese herbal formula TXYF consists of four Chinese herbs: *Atractylodes macrocephala Koidz.*, *Paeonia lactiflora Pall**.*, *Citrus × aurantium L**.*, and *Radix saposhnikoviae*. It has been used for diarrhea for hundreds of years and may have a potential benefit in treating adults with IBS-D, but due to lack of high-quality evidence, we designed a randomized, multiple-blind, placebo-controlled trial to evaluate its therapeutic effects and safety. This trial will provide important data to guide the clinical practice of TXYF for the treatment of IBS-D in adults.

**Trial registration:**

ISRCTN registry ISRCTN12453166. Registered on 23 March 2021.

## Introduction

Irritable bowel syndrome (IBS) is a functional gastrointestinal disorder, with a worldwide prevalence of approximately 11% [1]. The symptoms of IBS include chronic, recurrent, abdominal pain and discomfort, and altered bowel habits that occur in the absence of other organic gastrointestinal diseases [2]. It significantly reduces the quality of life of patients, their partners and caregivers, and affects daily activities and mental health [3, 4]. The underlying cause of IBS is thought to be multi-factorial, including: genetic factors, early life experience, psychological factors, prior gastroenteritis, food intolerance, and previous medication use [2, 5–8]. Based on the predominant stool patterns according to Rome VI criteria [9], IBS is classified into the following four types: constipation-predominant irritable bowel syndrome (IBS-C), diarrhea-predominant irritable bowel syndrome (IBS-D), mixed irritable bowel syndrome (IBS-M), and undefined irritable bowel syndrome. Of these, IBS-D is the most common type and accounts for up to 40% of patients with IBS [1, 10]. The specific pathogenesis of IBS has not been clarified clinically, and studies have shown that it may be related to brain and bowel dysfunction, gastrointestinal motility disorders, visceral hypersensitivity, psychosocial problems, and intestinal flora disorders [1, 11]. The treatment strategy of IBS-D includes antispasmodics for abdominal pain, antidiarrhoeals, nutritional intervention, and psychotherapy, but no specific therapeutic drugs that are able to treat all the symptoms have been found [12]. Some routine pharmacotherapies (e.g., antispasmodic drugs and antidiarrheal drugs) and alternative treatments (e.g., hypnotherapy and psychotherapy) [13] have been tried but have failed to achieve the desired clinical therapeutic effects.

IBS-D belongs to the category of diarrhea in traditional Chinese medicine (TCM) [14]. TCM may have potential in the treatment of IBS-D. Its therapies include oral traditional Chinese herbal formulas, external Chinese medicine treatments, and oral Chinese patent medicines. The most commonly used Chinese herbal formula is Tongxie Yaofang (TXYF) [15]. Chinese herbal formula TXYF was first recorded in the book named *Danxi Xinfa*, which is a comprehensive medical book edited in Yuan Dynasty (1271–1368) [16]. TXYF consists of four Chinese herbal medicines including *Bai Zhu (白术, Atractylodes macrocephala Koidz.)*, *Bai Shao (白芍,*
*Paeonia lactiflora Pall**.)*, *Chen Pi (陈皮,*
*Citrus × aurantium L**.)*, and *Fang Feng (防风, Radix saposhnikoviae)*. Clinically, TXYF usually has two dosage forms: granules and decoction. A series of studies have shown that TXYF can treat IBS-D by regulating the brain-gut axis, protecting the permeability of the intestinal mucosa, improving visceral hypersensitivity, and improving the body’s immune function [17–20]. Previous clinical trials [14, 21–24] have also demonstrated that TXYF is effective and safe for the treatment of IBS-D. However, to our knowledge, most trials have not been rigorously designed, especially in terms of the lack of randomization, blind and placebo control [14].

This randomized, multiple-blind, placebo-controlled trial is designed to evaluate the therapeutic effects and safety of TXYF in adults with IBS-D.

## Methods/design

### Study design

This is a randomized, multiple-blind, placebo-controlled superiority trial, and the protocol for this trial has been prepared following the Standard Protocol Items: Recommendations for Interventional Trials (SPIRIT) guidelines (see Additional file 1) [25]. The eligible participants will be allocated randomly into the experimental or placebo control group in a ratio of 1:1. Both groups will have an 8-week intervention followed by a 3-month follow-up period. This trial protocol has been registered in the ISRCTN registry (Reference number: ISRCTN12453166) on the 23 March 2021. A flow diagram of the trial is shown in Fig. 1.

**Fig. 1 Fig1:**
[figure not shown]
Study flow chart

### Trial setting

We will recruit 96 IBS-D participants from outpatient or ward of a hospital in Beijing, China: Fangshan Hospital of Beijing University of Chinese Medicine (FSH-BUCM).

### Participants

#### Recruitment

Participants will be recruited through e-posters on social media (e.g., WeChat Moments) or posters in the hospital. The poster/e-poster information will include a brief description of the participants who would be eligible and details of activities and necessary contributions as participants in the trial. Participant expressing an interest to take part will have the opportunity to talk with the researchers who will introduce the trial protocol as well as the benefits and risks to each enrolled participant, and informed consent form will be mandatory before the patient is enrolled in the trial. The compliance of the participants will be improved by regular telephone follow-up.

#### Participant inclusion criteria

The included participants must meet all the following criteria: (a) patients aged between 18 and 65 years, male or female; (b) patients who meet IBS-D Rome IV diagnostic criteria [9]; (c) patients who meet Liver Depression and Spleen Deficiency Syndrome (Ganyu Pixu Zheng) from the diagnostic criteria for TCM syndromes (2017) [26]; (d) irritable bowel syndromes symptom severity score (IBS-SSS) ≥ 75 points; (e) patients who have not taken any medications related to the treatment of IBS-D at least 1 week before enrolling the trial and have not participated in other ongoing trials; (f) patients who have had a colonoscopy within 1 year and had an examination report; (g) patients who have accepted to participate in the trial voluntarily and have signed the informed consent form. The informed consent process complies with Good Clinical Practice (GCP); (h) long-term (at least 6 months) residence in the place where the treatment is given.

#### Participant exclusion criteria

Patients who meet any of the following items will be excluded: (a) IBS patients with alternating diarrhea and constipation (relying on patients recall); (b) patients with severe tumors or organic lesions in the heart, liver, or kidney; (c) patients with severe mental illness or language disorders that affect communication; (d) patients with severe tumors or organic lesions in gastrointestinal tract, such as pancreatitis, history of colon or rectal cancer, intestinal tuberculosis, ulcerative colitis or Crohn’s disease; (e) patients with metabolic diseases affecting gastrointestinal motility, such as hyperthyroidism; (f) those who with an allergic constitution or allergic to the composition of the studied medication; (g) patients with a history of gastrointestinal surgery; and (h) pregnant or lactating women and women planning to have a child or fertility treatment.

#### Criteria for participants who discontinue the trial

If a participant experiences aggravation of their disease, complications or serious adverse events, and the researcher judges that the participant is not suitable to continue the treatment, the patient should be allowed to discontinue. For participants who discontinue the trial, the researcher should record in detail the time and reason for discontinuing in the case report form (CRF).

### Intervention

#### The experimental group

Participants will take TXYF granules manufactured by Anhui Jiren Pharmaceutical Co., Ltd. (Anhui, China). They will be instructed to take the granules orally before meals, one bag (3.7 g) twice daily, for 8 weeks. The granules are produced from four Chinese herbal pieces: *Bai Zhu (白术, Atractylodes macrocephala Koidz.)*, *Bai Shao (白芍,*
*Paeonia lactiflora Pall**.)*, *Chen Pi (陈皮,*
*Citrus × aurantium L**.)*, and *Fang Feng (防风, Radix saposhnikoviae)*. According to the records on the dosage of four Chinese herbal pieces from TXYF in *Danxi Xinfa* and the extraction rate of effective components in the process of granules production, we have determined the daily dosage of TXYF granules to be taken. A diagrammatic sketch of the production process of Chinese medicine decoction pieces into granules is presented in Fig. 2.

**Fig. 2 Fig2:**
[figure not shown]
A diagrammatic sketch of the production process of Chinese medicine decoction pieces into granules

#### The control group

Participants will take TXYF placebo granules manufactured by Anhui Jiren Pharmaceutical Co., Ltd. (Anhui, China), take orally before meals, one bag (3.7 g) twice daily, for 8 weeks. The placebo is made of lactose, flour, sucrose, edible caramel pigment, bitter and aspartame, etc. Its appearance, taste, and specification are consistent with TXYF granules to the greatest extent possible. In terms of outer packing, the placebo and TXYF granules will be exactly the same.

#### Concomitant treatment

If the participant is unable to tolerate the IBS-D symptoms or is dissatisfied with the therapeutic effects of TXYF during the treatment, pinaverium bromide (the first-line recommended drug in American Gastroenterological Association Institute Guidelines on the Pharmacological Management of Irritable Bowel Syndrome [27]) or other medications recommended by guidelines will be allowed to be taken by the patient. No matter what medications the patient uses, the medication’s name, dosage and duration of administration will be recorded in detail in CRF.

#### Experimental medication preparation and quality control

Anhui Jiren Pharmaceutical Co., Ltd. (Anhui, China) is responsible for the production and quality control of TXYF granules and placebo.

### Randomization, allocation concealment, and blinding

A sequence of random numbers was generated by the R version 4.0.3 software and performed by the Centre for Evidence-based Chinese Medicine, Beijing University of Chinese Medicine (CEBCM-BUCM). The eligible participants will be randomly assigned to either the experimental (TXYF) or control (placebo) group in a ratio of 1:1. Allocation concealment will be done, using the method of “coding the drug packaging,” to minimize selection bias [28–30]. The sequence of randomization and allocation will be kept blind at all times to all participants and clinician until the trial has been completed. The placebo appearance, taste, and specification will be similar to TXYF granules as far as possible. The placebo and TXYF granules will have exactly the same outer packaging. Only the designated persons ([name] and [name] from the CEBCM-BUCM) will have access to the sequence of randomization and allocation during the trial, and they will not share the relevant information until such a time where the study has concluded and all of the data has been collected (unless serious adverse event occurs).

During the trial, if a participant experiences a serious adverse event or needs emergency rescue, the clinician can request the clinical research associate or the main researcher to disclose the intervention the participant has received. Once it is decided to disclose the intervention the participant has received, the participant will be recorded as a withdrawal case. Once the number of participants whose intervention is disclosed reaches or exceeds 20% of the required sample size, the trial can be considered to be a failure in blinding the participants and clinicians [31].

Furthermore, the outcome assessors collecting the outcome data were blinded to the allocation of the interventions too, throughout the study. Before completing the statistical analysis, the statistical analyst is also unable to know whether the participant is taking TXYF or placebo.

### Outcomes

We referred to the 2017 Consensus on Diagnosis and Treatment of Irritable Bowel Syndrome in TCM [26], outcomes in the relevant registered or published clinical trials, as well as the actual clinical diagnosis and treatment of IBS-D, to determine the outcomes to be evaluated in our this trial.

#### Primary outcomes

The degree of IBS symptom severity, measured using the scale of irritable bowel syndromes symptom severity score (IBS-SSS) [32]. The disease severity will be divided into four levels base on IBS-SSS: normal (the score < 75), mild (75 ≤ the score < 175), moderate (175 ≤ the score < 300), and severe (the score ≥ 300). If the disease severity remains at the original (baseline) level or changes to higher level (e.g., from mild to moderate) after treatment, it will be judged as no response; otherwise, it will be considered response. The response rate = (total number of participants − number of no response participants)/total number of participants × 100%. Finally, we will not only compare the scores after treatment between groups, but also compare the response rate.

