### Sample size

According to previous studies [37], it is estimated that TXYF can produce efficacy response (according to IBS-SSS) in 73% of participants with eight weeks treatment. Under the same treatment duration and evaluation criteria used in this trial, no results of placebo treatment of IBS-D were found. However, based on previously published relevant studies [38, 39], we expect TXYF to have a 30% higher response rate than placebo in the primary outcome, and superiority margin is expected to be 10% (*δ* = 10%). The ratio of the TXYF group to the control group was 1:1. So, the total sample size of 96 is based on the following formula [40], when *α* = 0.05, power = 0.8, and the estimated loss of participants is 10% [31]. That is, the number of participants to be enrolled in the trial should be 48 in each group.
$$ n={\left({Z}_{1\hbox{-} \alpha / 2}+{Z}_{1\hbox{-} \beta}\right)}^2\left[{P}_1\left( 1\hbox{-} {P}_1\right)+{P}_2\left( 1\hbox{-} {P}_2\right)\right]/{\left(P 1\hbox{-} P 2\hbox{-} \delta \right)}^2 $$

Where *n* denotes the sample size of each group, the value of *Z*_*1-α*_ and *Z*_*1-β*_ needs to consult the Z value table, *P*_*1*_ denotes the rate of the experimental group and *P*_*2*_ represents the rate of the control group, and *δ* represents the superiority margin. Therefore, when calculating the sample size of this trial, the value of *Z*_*1-α*_ is 1.96, the value of *Z*_*1-β*_ is 0.842, the value of *P*_*1*_ is 73%, the value of *P*_*2*_ is 43%, and the value of ***δ*** is 10%.

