#### Principle of analysis

All analyses will be by the intention-to-treat (ITT) principle which included all randomized patients who received the TXYF or its placebo and returned for at least one follow-up appointment. The per-protocol set (PPS) analysis for the primary outcomes is being conducted in conjunction with the ITT analysis. When the results of ITT and PPS analysis are conflict, the results of ITT analysis will be given preference. When the results of ITT and PPS analysis are consistent, the reliability of the results can be increased. ITT will be used for the analysis of baseline characteristics, and safety set (SS) will be used for the safety evaluation.

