#### Statistical description and statistical analysis methods

With regard to continuous outcomes, Q-Q plots will be used to evaluate normality assumptions. Continuous outcomes conforming to the normal distribution will be presented as mean ± standard deviation (SD) and non-conforming to the normal distribution will be presented as median and interquartile range (IQR) [41]. For both primary continuous outcomes and secondary continuous outcomes, simple or multiple linear regression will be applied to estimate the difference between TXYF group and placebo group. Two preadjusted analyses will be conducted, if appropriate. The first preadjusted regression analysis included only baseline variables (e.g., age, gender, smoking and drinking). The second preadjusted analysis will also adjust for concomitant treatment, a variable thought to be associated with outcome but not affected by treatment allocation.

Categorical data will be expressed by the number and percentage of occurrences. For primary and secondary categorical outcomes, differences will be compared using chi-squared tests and, if appropriate and necessary, logistic regression. The preadjusted analyses will be conducted that adjust for the same covariates as those described for the continuous outcomes.

Estimates of treatment effect will be reported with 95% confidence intervals. Two-tailed *P*-values ≤ 0.05 will be considered statistically significant.

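### Two primary IBS-SSS comparisons share one unadjusted 0.05 threshold with no decision rule; if either may carry the trial, the two-sided false-positive rate is about 8–10%

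*Protocol article*

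**What the plan says.** The abstract gives one construct: "The primary outcome will be the degree of IBS symptom severity", measured on the IBS-SSS. The Primary outcomes section defines four severity bands and counts a participant as a responder if the band improves after treatment. It then adds: "we will not only compare the scores after treatment between groups, but also compare the response rate".

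The section Statistical description and statistical analysis methods refers to primary continuous outcomes and to primary categorical outcomes, so both comparisons have primary status.

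- For the score: "simple or multiple linear regression will be applied to estimate the difference between TXYF group and placebo group".
- For the response rate: "differences will be compared using chi-squared tests and, if appropriate and necessary, logistic regression".
- For adjustment: "Two preadjusted analyses will be conducted, if appropriate".
- For every test, the rule is that two-tailed P-values "≤ 0.05 will be considered statistically significant".

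The Sample size section uses the response rate only, with α = 0.05: "we expect TXYF to have a 30% higher response rate than placebo in the primary outcome". It also sets a superiority margin of 10 percentage points.

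The one precedence rule given concerns analysis sets: "When the results of ITT and PPS analysis are conflict, the results of ITT analysis will be given preference".

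**The concern.** The 0.05 in the sample size calculation belongs to one test, but the outcome and methods sections set up two primary tests at that level. Without a rule linking them, a significant result on either could be presented as the trial's primary success. The stated 5% would then not be the error rate of the trial's main claim.

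A second problem does not depend on any error-rate calculation: the two measures can disagree. Response requires crossing a band boundary. A fall from 290 to 180, which is 110 points, stays within the moderate band and is no response. A fall from 180 to 170, which is 10 points, moves from moderate to mild and is a response. The score and the response rate can therefore point to different conclusions, and the text does not say which one decides.

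**Working it through.** **Inputs from the protocol article**

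- Two primary comparisons (Primary outcomes).
- Two-sided threshold of 0.05 for each, critical value 1.96 (statistical methods; Sample size).
- P1 = 73%, P2 = 43%, margin 10 points, 48 per group, 10% loss (Sample size). The loss leaves 48 × 0.9 ≈ 43 evaluable per group.

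**Input not in the protocol article**

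- The correlation ρ between the two test statistics. It is assumed below and shown over a range.

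**1. The plan's own figure.** No trial-wide error rate is stated. The only related figure is the sample size. Its formula gives (1.96 + 0.842)² × [0.73×0.27 + 0.43×0.57] / (0.73 − 0.43 − 0.10)² = 7.851 × 0.4422 / 0.04 = 86.8 per group, against 48 per group stated. That mismatch is a separate matter. What counts here is that every input is a response rate and the score does not enter.

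**2. Either test counts, both against zero difference.** With no effect, P(at least one significant) = 1 − P(|Z₁| < 1.96 and |Z₂| < 1.96). For independent tests this is 1 − 0.95² = 9.75%. For correlated tests the bivariate normal distribution gives the second column. The third column counts only results that favour TXYF: 1 − P(Z₁ < 1.96 and Z₂ < 1.96), with both statistics signed so that positive favours TXYF.

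| ρ | Either test, two-sided | Falsely favouring TXYF |
|---|---|---|
| 0 | 9.75% | 4.9% |
| 0.5 | 9.1% | 4.5% |
| 0.8 | 7.8% | 3.9% |
| 0.9 | 7.0% | 3.5% |
| One test alone | 5% | 2.5% |

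**3. A plausible ρ.** A simulation with no effect derived response from the protocol's severity bands. It used 43 or 48 per group and 6,000 runs per scenario. The assumed inputs, none of them in the protocol, were baseline mean 240, SD 75, a baseline-to-post correlation parameter of 0.2 to 0.7 and a mean fall of 50 to 90 points. The two effect estimates correlated at about 0.40 to 0.57 in absolute value. The either-test rate was 8.6% to 9.9%, with a Monte Carlo standard error of about 0.4 points.

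**4. Both must succeed.** P(both) = 5% + 5% − P(either). At ρ = 0.5 this is 10% − 9.1% = 0.9%. The simulation gave about 1%. There is no inflation under this rule.

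**5. Response test against the 10-point margin.** Suppose both groups truly respond at 43%, with 43 per group. The standard error is √(2 × 0.43 × 0.57 / 43) = 0.107. A superiority claim needs Z > 1.96 + 0.10/0.107 ≈ 2.90, which has probability about 0.2%. The either-test rate is then at most 5% + 0.2% = 5.2%.

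**The case against.** The strongest objection is that the inflation is conditional. The protocol says that both measures will be compared; it does not say that either one suffices. If both were required, the error would be far below 5%. This stands, and the 8–10% has to be stated as conditional.

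The margin also matters. The Sample size section defines superiority with a 10-point margin, and a response test built on it would add almost nothing to the error. The methods section, however, names a chi-squared test, which points to a test of zero difference. The text leaves both readings open. It is also true that the two-sided figure includes results favouring placebo, so the chance of wrongly favouring TXYF is about half of it.

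A further objection is that order and alpha allocation are commonly left to the statistical analysis plan, which the article cites and which is not shown. That plan may contain a rule. The point survives because it rests on what the protocol states: two primary comparisons, one flat threshold and sizing on only one of them.

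Three stronger readings are tempting but not supported:

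- **An error rate of 11% or more, from counting adjusted models.** The adjusted analyses are conditional on being appropriate, and any figure for them depends on covariate and outcome assumptions that the protocol does not give.
- **A contradiction between the abstract and the outcome section.** Both name severity on the IBS-SSS. The outcome section summarises that one construct in two ways.
- **The per-protocol analysis as another chance of success.** The Principle of analysis section already puts ITT first.

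**Conclusion.** The point holds in conditional form. The protocol fixes two primary comparisons at an unadjusted two-sided 0.05, sizes one of them, and states no rule that joins them.

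If success on either is enough and both are tested against zero difference, the two-sided false-positive rate is about 8–10%, or about 4–5% against 2.5% for falsely favouring TXYF. The range reflects an assumed correlation of 0 to 0.8. The rate stays near 5% if the response test uses the 10-point margin, and falls well below 5% if both must succeed. A reader might infer that the trial's error rate simply is 8–10%; the text does not commit to the either-suffices rule that this would need.

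Under every one of these readings, the protocol text does not say what is concluded when the score and the response rate disagree. The matter should be settled before unblinding.

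**What to change.** Name the week-8 response rate, the endpoint on which the trial was sized, as the single primary outcome. Give it one named primary analysis on the ITT set, and say whether the test is against zero or against the 10-point margin. Make the week-8 IBS-SSS score the first key secondary outcome, tested at two-sided 0.05 only if the response rate is significant. Label the other adjusted models as sensitivity analyses. ITT precedence over per-protocol is already in place and needs no change.

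The cost is more than wording. Recruitment began in April 2021, and the Ethics section requires protocol revisions to go to the ethics committee and the registry. An amendment to the protocol, the analysis plan and the registry entry is therefore needed before unblinding.

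The statistical cost is that the score cannot be claimed as confirmatory if the response rate fails. That is a real risk if the margin is used: with the planned rates, power is Φ(0.20/√(0.4422/n) − 1.96), about 55% with 48 per group and 50% with 43.

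Requiring both measures to succeed, or testing each at 0.025 (at most 5% overall; 1 − 0.975² = 4.94% if independent), would also control the error. Either is acceptable if the choice is written down before unblinding.
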